**Methods and analysis:**

VPT and FT dyads will be enrolled at birth, and the former will be randomly allocated to one of two arms: VF intervention or care as usual. Short-term effectiveness will be assessed through ratings of mother–infant interaction videotaped before and after the VF intervention or care as usual. Mothers of VPT and FT infants will report on their mental state, parenting stress and bonding, and infant temperament and sensory profile at 3 and 6 months (corrected age, CA). At 9 months CA, all dyads will participate in a lab-based EEG-hyperscanning paradigm to assess brain-to-brain co-regulation through phase-locking value (PLV) and other explorative indices.

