#### Study timeline

The 2-BRAINED study features five data collection waves (see Figure 1). The VF intervention is delivered after wave T1 (NICU discharge) and before wave T2 (3 months CA) to subjects allocated to the VPT-VF arm. The EEG-hyperscanning task will occur for all subjects at wave T4 (9 months CA) and will feature the videotaping of mother–infant interaction according to a modified Face-to-Face Still-Face (FFSF) procedure (Tronick et al., 1978) and the simultaneous EEG data collection from both the interactive partner. At each wave, parents will receive questionnaires by email using REDCap.^1^

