##### Intervention details

The remote VF intervention has been adapted according to previous research from our group (Grumi et al., 2021). It comprises six weekly 1-h sessions organized in two subsequent phases: four *sharing the focus* sessions and two *integration* sessions. *Sharing the focus* sessions are dedicated to the discussion between the psychologist and the mother of specific themes related to parenting and parent–infant interaction: physical stimulation, responsiveness, teaching, and parenting experience (see Table 1). During these sessions, a purposively trained psychologist invites the mother to jointly review and discuss brief clips obtained from the pre-intervention videotaped interaction, usually starting from potential curiosity, comments, or requests from the mother herself. The goal of the *sharing of the focus* sessions is to develop insights about the infants’ behavioral signals, how to respond contingently and appropriately, how to promote emotion regulation, and how to sustain cognitive and behavioral achievements. In the subsequent two *integration* sessions, the mother plays with the infant while the psychologist provides guidance based on insights co-developed during the previous four sessions. The goal is to promote a pragmatic translation of the insights into interactive skills.

**Table 1 tab1:** Description of the thematic focus of the four *sharing the focus* sessions of the video-feedback (VF) intervention.

Thematic cluster	Key topic	Goal
Sensory stimulation and regulation	Sensory channels	Highlighting infant preference or avoidance of specific sensory channels and stimuli.
	Intensity of stimulation	Regulating intensity of physical stimulation and understanding infant sensory thresholds.
	Affective social touch	Facilitating parental affective touch to promote infant state regulation, postural stability, and attention orientation.
Nurturing and sensitive caregiving	Parental sensitivity	Promoting parental perception, interpretation, and appropriate responsiveness to infant communicative signals.
	Sense of agency	Detecting and supporting the infant’s interactive initiatives (e.g., vocalizations and attention orienting).
	Exploration and safety	Supporting the infant exploration of the environment and building safety and trust in parental secure base.
	Rhythm and reparation	Facilitating the emergence of a proto-conversational rhythm in the dyad and supporting reparative actions of interactive perturbations.

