Cognitive sensitivity and scaffolding	Attention skills	Supporting and scaffolding infant sustained and focused attention to the physical and social environment.
	Modeling and guidance	Providing a model to foster observational learning and the functional use of tools and toys.
	Proximal development zone	Improving caregiver awareness of the cognitive abilities of the infant to make appropriate play proposals and support infant emerging abilities.
Parenting experience and mental state	Mind-mindedness	Improving awareness about parental representations of the infant mind and keeping high levels of curiosity about infant behaviors.
	Self-care and self-regulation	Highlighting the importance of parental psychological wellbeing and reflective functions; promoting parental psychological self-care and compassion.
	Self-efficacy	Strengthening the caregiver’s sense of efficacy as a parent and nourishing trust in the parent’s own experience and mental representations of the infant.

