### Plan of statistical analyses

#### Preliminary analyses

##### Specific aim 1

General linear models (GLMs) will be carried out to compare VPT and FT dyadic brain-to-brain co-regulation indices during the experimental procedure phases. Theoretically relevant (e.g., gestational age) and statistically identified (e.g., any variable significantly linked with the outcome variables) confounding variables will be controlled for in the analytical model.

##### Specific aim 2

Separate analyses of variance (ANOVA) will be used with dyadic brain-to-brain co-regulation indices as the dependent variable and groups (FT, VPT-VF, and VPT-CU) as the independent variable. Theoretically relevant (e.g., gestational age) and statistically identified (e.g., any variable significantly linked with the outcome variables) confounding variables will be controlled for in the analytical model.

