##### Additional aims

Models to track early developmental trajectories will be estimated in Mplus by latent class growth analysis with inter-individual variations in time of assessment and mixed-effect linear models with repeated measures to assess group differences in rates of temperament, emotional, and sensory profiles.

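### The Aim 2 covariate rule is not limited to pre-intervention variables, so it allows part of the video-feedback effect to be adjusted away in the randomised VPT-VF versus VPT-CU contrast

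*Protocol article*

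**What the plan says.** Under Plan of statistical analyses, Specific aim 2, the model is described thus: "Separate analyses of variance (ANOVA) will be used with dyadic brain-to-brain co-regulation indices as the dependent variable", with the three groups FT, VPT-VF and VPT-CU as the factor. Two kinds of covariate enter. The first is theoretically relevant variables, with gestational age as the example. The second is given by a data-driven rule: "statistically identified (e.g., any variable significantly linked with the outcome variables) confounding variables will be controlled for in the analytical model". The same sentence appears under Specific aim 1.

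Study timeline fixes when treatment occurs: "The VF intervention is delivered after wave T1 (NICU discharge) and before wave T2 (3 months CA"). T2, T3 and T4 are therefore all post-intervention. The Abstract says that mothers "will report on their mental state, parenting stress and bonding, and infant temperament and sensory profile at 3 and 6 months", and Table 2 gives the wave of each questionnaire.

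Table 1 (Intervention details) lists what the sessions aim to change. One goal reads "Highlighting the importance of parental psychological wellbeing and reflective functions; promoting parental psychological self-care and compassion"; another reads "Regulating intensity of physical stimulation and understanding infant sensory thresholds".

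**The concern.** In the VF versus CU comparison, allocation is random, so a variable measured after allocation that VF may have changed is not a confounder. It may be a step on the path from VF to the EEG outcome. The only test the article gives for entry is a significant association with the outcome, and a mediator passes that test.

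The article makes both links of such a path plausible. Table 1 targets parental wellbeing, and Additional exploratory aims expects co-regulation to depend on affective symptoms, parenting stress, temperament and sensory profile. Additional aims also treats some of these measures as responses, with models "to assess group differences in rates of temperament, emotional, and sensory profiles".

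If a mediator is selected, the group coefficient no longer estimates the total effect of offering VF. It estimates what remains after removing the part that works through that variable, and randomisation alone no longer protects it. Aim 2 is also the aim on which the sample size was set.

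**Working it through.** **Step 1. Timing of the candidate variables** (Table 2 against Study timeline and Table 1).

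| Questionnaire | Waves | Relative to VF | Match with a VF session goal |
|---|---|---|---|
| PSS-NICU | T1, VPT only | before | not applicable |
| STAI-Y | T2, T4 | after | parental wellbeing: clear |
| BDI-II | T2, T4 | after | parental wellbeing: clear |
| PSI-SF | T2, T3, T4 | after | parental wellbeing, self-efficacy: clear |
| SP-2 | T2, T3, T4 | after | sensory theme: possible |
| IBQ-R | T2, T3, T4 | after | no matching theme |

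Five of six are collected only after VF. The behaviour codes from the 9-month session are also post-VF. Demographic, neonatal and clinical chart variables (Measures) are further candidates and do not have this timing problem.

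**Step 2. The plan's own sample size.** For a one-way ANOVA with three groups, f = 0.25 and alpha = 0.05, the noncentrality is f²N = 0.0625 × 159 = 9.94 on (2, 156) degrees of freedom. Power is 0.805; N = 156 gives 0.797. The stated 159 (53 per arm) reproduces and is not in dispute. I use 53 per arm below.

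**Step 3. VF versus CU without post-VF adjustment.** Assume a total effect d = 0.5 SD (not in the article). The standard error is √(2/53) = 0.194, so d/SE = 2.57. The exact two-sided two-group power is 0.722.

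**Step 4. One post-VF covariate M admitted by the stated rule.** Let G be the arm, with M = aG + u and Y = c′G + ρM + e, and unit within-arm SDs. Here a is the shift in M caused by VF and ρ is the within-arm correlation of M with Y. Then:

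- total effect: d = c′ + ρa
- estimate adjusted for M: d − ρa
- SE of the adjusted estimate: √(2/53) × √(1 − ρ²) × √(1 + a²/4)

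M enters only if its pooled correlation with Y has p < 0.05, as the rule says. For a = 0.6 the correlation follows from the mediated share: ρ = share × 0.5 / 0.6. Power comes from simulating the rule.

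| Shift a | ρ | Adjusted estimate | SE if adjusted | Power under the rule |
|---|---|---|---|---|
| 0 | 0.3 | 0.50 | 0.185 | about 76% |
| 0.1 | 0.3 | 0.5 − 0.03 = 0.47 | 0.186 | about 71% |
| 0.2 | 0.3 | 0.5 − 0.06 = 0.44 | 0.186 | about 64% |
| 0.3 | 0.3 | 0.5 − 0.09 = 0.41 | 0.187 | about 57% |
| 0.6 (25% mediated) | 0.21 | 0.5 − 0.125 = 0.38 | 0.198 | about 48% |
| 0.6 (50% mediated) | 0.42 | 0.5 − 0.25 = 0.25 | 0.184 | about 27% |
| 0.6 (75% mediated) | 0.63 | 0.5 − 0.375 = 0.13 | 0.158 | about 12% |

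The power figures carry about a percentage point of simulation error. In a separate grid with ρ = 0.3 or 0.5 and 25% or more of the effect mediated, the rule admitted M in 95–100% of simulated trials. The significance filter is therefore little protection.

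**Step 5. Null check.** With 10 to 44 pure-noise candidates, type I error under the rule stayed at 0.048–0.051. The problem is adjustment for mediators, not inflation of alpha.

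**The case against.** The strongest reply is that the clause speaks of confounding variables, and a mediator is not one. An analyst who takes the word seriously would exclude it. That helps only in part, because the only criterion given is significant association with the outcome, and it does not separate the two.

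Three further objections stand and limit the point:

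- **Post-VF does not mean mediator.** IBQ-R temperament matches no session theme, and SP-2 is a less clear target than parental distress. A later variable untouched by VF causes no bias and can raise power (about 76% at ρ = 0.3 and 83% at ρ = 0.5, against 72%).
- **A reader might infer that nearly all candidates are post-VF.** Counting questionnaire scores by wave gives 41 of 44 (PSS-NICU 3, SP-2 14, STAI-Y 4, BDI-II 2, PSI-SF 12, IBQ-R 9, with only the 3 PSS-NICU scores at T1). The article does not support that as a share of all candidates. The rule covers any variable, including chart data. Bonding and perceived staff support are mentioned elsewhere but are absent from Table 2 as read, so the number of pre-VF candidates is unknown.
- **The lower rows of the table are severe.** A 0.6 SD shift in the covariate exceeds the 0.5 SD effect assumed on the outcome itself. The milder rows are needed for a fair picture.

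It can also be said that the final covariate list belongs in an analysis plan. That would answer a missing list. It does not answer a stated rule that admits the wrong kind of variable.

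**Conclusion.** The point holds as a defect in a stated rule. As written, the Aim 2 rule allows post-intervention variables, including measures of parental distress and parenting stress that VF plausibly changes, into the randomised VF versus CU contrast.

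A reader might infer that the rule will remove the treatment effect. The article does not support that. The loss depends on VF shifting a selected variable, and the article gives neither that shift nor the correlation with the EEG indices. Under the assumptions above, the estimate runs from 0.50 SD (no mediation, no bias) through 0.47 to 0.41 SD for shifts of 0.1 to 0.3 SD, down to 0.13 SD in the most severe case shown. Attenuation toward zero assumes that direct and mediated effects have the same sign. The power figures are for a two-group test with one covariate, not for the planned three-group ANOVA.

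A reader might also infer that the clause is wrong throughout. It is not: the VPT versus FT comparison in Aim 1 is not randomised, and confounding there is a real issue.

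**What to change.** For the VF versus CU contrast in Aim 2, replace the data-driven clause with a prespecified covariate set restricted to variables measured at or before T1, the same for every co-regulation index. Infant sex and gestational age are examples. Suitable wording would be: *The VPT-VF versus VPT-CU contrast will be adjusted only for the following variables, all measured at or before T1: [list]. No variable measured at T2 or later will be used as a covariate in this contrast.*

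PSS-NICU and the T1 interaction rating are attractive baseline covariates. PSS-NICU is collected only in VPT dyads, and T1 videotaping is described only for the VPT arms. They can therefore be added only in a model confined to those two arms, not in the stated three-group ANOVA. Choosing them means specifying that model, which is more than a change of wording.

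Use the T2–T4 questionnaires and the 9-month behaviour codes only in analyses labelled as mediation or exploratory. Specify confounders for Aim 1 separately, since this change does not cover it.

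The cost is a short edit and no new data. The downside is small: a predictive variable outside the list, or one measured later, is not used, and its gain in precision is forgone.

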## Methods and procedures

### Study design and procedures

The 2-BRAINED project is a randomized-controlled trial (RCT) with three arms. The first arm includes VPT infants and their caregivers randomly allocated to the intervention arm (VPT-VF). The second arm includes VPT infants and their caregivers randomly allocated to the care as usual arm (VPT-CU). This arm will act as a control group matched to preterm conditions of VPT-VF. The third arm includes FT infants and their caregivers and will act as an additional control group unmatched by preterm conditions. Both VPT-CU and FT arms will receive no VF intervention.

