### Statistical power and sample size estimates

The sample size has been estimated according to over-arching Aim 2, setting parameters as follows: medium effect size, *f* = 0.25, *alpha* = 0.05, *beta* = 0.20, number of groups = 3 (VPT-VF, VPT-CU, and FT). The procedure yielded a total sample size of 159 subjects (53 subjects per RCT arm). Nonetheless, considering the longitudinal nature of the study and the attrition rate related to EEG tasks with infants, an oversampling of *n* = 80 (~ +50%) subjects per RCT arm was planned to secure the minimum sample size for appropriately powered statistical analyses.

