### Sources of bias and mitigation strategies

The heterogeneity of VPT infants’ conditions should not be underestimated. Even in the absence of severe comorbidities and brain injuries, the experience of NICU hospitalization might be very different for each infant and their parents. To avoid extreme variations, the gestational age range will be constrained between 28 and 35 weeks. Moreover, stress related to the NICU environment will be evaluated and quantified with a well-validated questionnaire (Miles et al., 1993). Selection issues might affect random allocation plans in RCT arms. The allocation to VPT-VF and VPT-CU arms will occur by using an automatically generated list of binary codes that will be consecutively matched with the enrolled families across consecutive sampling. This will reduce the risk of self-selection. To further avoid confounding by infant sex and assure sex distribution balancing, the random allocation will be stratified by infant sex by *post-hoc* controls every 20 enrollments. Parental gender will also be unconstrained, inviting the primary caregiver—and not explicitly the mother—to participate in the study, VF intervention, and observational procedures. EEG procedural steps and artifacts might easily result in the loss of subjects in a longitudinal study; a 50% oversampling was planned to achieve the minimum sample size for adequately powered statistical analyses.

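### Infant sex is the stratification factor for the two very preterm arms, but the Aim 1 and Aim 2 covariate rule neither names nor guarantees it, so the analysis need not match the allocation

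*Protocol article*

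**What the plan says.** **Allocation.** The section on sources of bias and mitigation strategies describes how the two very preterm arms are formed: "The allocation to VPT-VF and VPT-CU arms will occur by using an automatically generated list of binary codes". It then singles out one factor: "To further avoid confounding by infant sex and assure sex distribution balancing, the random allocation will be stratified by infant sex", maintained through checks after every 20 enrolments. No other balancing factor is named.

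**Full-term arm.** Under study design and procedures: "The third arm includes FT infants and their caregivers and will act as an additional control group unmatched by preterm conditions". These dyads are not randomised, and no sex matching or balancing is stated for them.

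**Models.** For Aim 1, "General linear models (GLMs) will be carried out to compare VPT and FT dyadic brain-to-brain co-regulation indices". For Aim 2, "Separate analyses of variance (ANOVA) will be used with dyadic brain-to-brain co-regulation indices as the dependent variable and groups (FT, VPT-VF, and VPT-CU"). Both aims carry the same covariate sentence: "Theoretically relevant (e.g., gestational age) and statistically identified (e.g., any variable significantly linked with the outcome variables) confounding variables will be controlled for". The rule has two routes into the model, one theoretical (gestational age is the only example) and one statistical (significant association with the outcome). Sex is named under neither.

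**The concern.** When allocation is stratified by a factor, the usual practice is to put that factor in the model, so that the standard errors reflect the design. Here the design section calls sex a confounder and the analysis section does not say what happens to it. Three things follow.

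- **Randomised contrast (VPT-VF v VPT-CU).** If sex is left out, its variance stays in the residual and the comparison loses a little precision.
- **Non-randomised contrast (VPT v FT).** The stratification gives no protection here. Any difference in the share of boys passes into the contrast unless the model adjusts for it.
- **Consistency.** Aim 2 uses a separate model for each index. If sex enters by the significance route, it may be in the model for one index and absent from the next, and that choice is made after the outcomes are seen.

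**Working it through.** **1. The plan's own figure.** The sample-size section gives "medium effect size, *f* = 0.25, *alpha* = 0.05, *beta* = 0.20, number of groups = 3" and a total of 159 (53 per arm). For a one-way ANOVA, power comes from the noncentral F distribution with df1 = 2, df2 = N − 3 and noncentrality f²N.
- N = 157: 0.7995. N = 158: 0.8022. N = 159: 0.8049.
- The smallest adequate N is 158, which becomes 159 with equal arms. The stated figure reproduces.

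**2. Cost of always including sex.** With one covariate, df2 falls from 156 to 155. If sex has no effect, power at N = 159 goes from 0.8049 to 0.8048. The required N stays 159.

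**3. Gain against the significance screen.** The documents give no sex effect on the phase-locking value (PLV) or any other index, so the boy-girl difference d (in within-sex SD) is assumed over a range. For a factor split about 50/50, the correlation with the outcome is ρ = d/√(d² + 4). Power with sex in the model uses f²/(1 − ρ²) and df2 = 155. The chance that sex passes a two-sided 5% screen comes from the noncentral t with 80 and 79 per sex. The loss from relying on the screen is approximated as gain × (1 − chance of selection).

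| d (SD) | ρ | Chance selected | Power, sex in | Gain over never in (points) | Loss under screen (points) |
|---|---|---|---|---|---|
| 0.1 | 0.05 | 10% | 80.6% | 0.1 | 0.1 |
| 0.2 | 0.10 | 24% | 80.9% | 0.4 | 0.3 |
| 0.3 | 0.15 | 47% | 81.4% | 0.9 | 0.5 |
| 0.4 | 0.20 | 71% | 82.1% | 1.6 | 0.5 |
| 0.5 | 0.24 | 88% | 83.0% | 2.5 | 0.3 |
| 0.74 | 0.35 | 99.6% | 85.5% | 5.0 | 0.02 |

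The last column peaks at about half a point, near d = 0.35.

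**4. Consistency between models.** Table 4 of the article lists three indices, and mainly two frequency bands are planned. At d = 0.3 the screen admits sex 47% of the time. For two outcomes with that effect and independent screens, the chance that one model contains sex and the other does not is 2 × 0.468 × 0.532 = 0.50. Positively correlated outcomes would disagree less often.

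**5. VPT v FT bias.** With sex omitted, bias = d × (difference in share of boys). The shares are also assumed.
- 0.3 × (0.60 − 0.50) = 0.030 SD
- 0.3 × (0.60 − 0.45) = 0.045 SD
- 0.5 × (0.60 − 0.50) = 0.050 SD

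A simulation (6,000 trials per scenario, 53 per arm, sex balanced between the VPT arms and free in FT) gave 0.030, 0.047 and 0.051 SD with sex never included. With inclusion only if significant it gave 0.010, 0.018 and 0.003 SD.

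**6. Type I error.** Five scenarios were simulated: these three, plus d = 0.3 and d = 0.5 with half boys in every arm. Under the significance screen, the nominal 5% test rejected in 4.5% to 5.2% of trials for VPT-VF v VPT-CU and in 4.7% to 5.4% for VPT v FT. The Monte Carlo standard error is √(0.05 × 0.95/6000) ≈ 0.3 points, so there is no sign of inflation.

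**The case against.** **Sex may enter without any test.** A reader might infer that the models admit sex only if it tests significant, or that group is the only committed term. The text does not support either reading. Confounders judged relevant on theory are also to be controlled for, gestational age is only an example, and the article itself calls sex a source of confounding. This objection stands. The point is that sex is neither named nor guaranteed, not that it is excluded.

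**Large effects would be caught.** A reader might also infer power gains of 5 to 10 points, or true test sizes of 2.4% to 4.0% for a nominal 5% test. Those figures compare sex always in with sex never in, and the plan never says sex is left out. A 5-point gain needs a boy-girl difference of about 0.74 SD, which even the screen would select 99.6% of the time. The test sizes also assume exact sex balance in the analysed set. That is not established, because balance is checked only every 20 enrolments and dyads can later be excluded for EEG quality. This stands too, and those figures should not be used.

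**The full documents may settle it.** An article condenses its protocol, and a complete covariate list is commonly left to the analysis plan. This stands in part: the absence of a list is not the point. The article does state a covariate rule, however. That rule contains an outcome-driven screen and leaves open the status of the one factor the allocation is stratified by.

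**Conclusion.** The point holds as a mismatch between design and prespecified analysis. Sex is the only named stratification factor, the FT arm has no stated protection against a sex imbalance, and the shared covariate rule leaves inclusion to judgement or to a p-value.

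Its size is modest. The precision at stake is at most about half a power point relative to the screen. The bias in the VPT-FT contrast is about 0.03 to 0.05 SD if sex is omitted and about 0.02 SD or less under the screen. Type I error is not inflated. These figures rest on assumed sex effects of 0.1 to 0.74 SD for power and 0.3 to 0.5 SD for bias, and on 45-50% boys in the FT arm against 50-60% in the VPT arms. None of these is given in the documents. A larger sex effect together with a larger imbalance would raise the bias when sex is omitted in proportion.

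The case for change therefore rests mainly on agreement with the allocation, on prespecification and on comparable models across indices. It is worth making because it costs almost nothing.

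**What to change.** In the plan of statistical analyses, add one sentence covering Specific aims 1 and 2, for example: *Infant sex, the stratification factor, is included as a fixed covariate in all Aim 1 and Aim 2 models for all indices, whatever its p-value.* The significance screen should play no part in that decision.

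The cost is that sentence and one residual degree of freedom (156 to 155 in the three-group model at N = 159). Sex is already recorded for the allocation, so no new data are needed, and the planned sample size is unchanged.

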## Study AIMS

### General and specific aims

The *2-Brain Regulation to Achieve Improved Neuroprotection during Early Development* (2-BRAINED) research project is funded by the Italian Ministry of Health under the Ricerca Finalizzata 2021 program (research line: Giovani Ricercatori, project code: GR-2021-12375213). It is aimed to assess brain-to-brain co-regulation patterns in dyads of VPT infants and their caregivers and further explore how an early VF intervention may facilitate specific inter-brain regulatory indices.

The first specific aim (Aim 1) is to assess the presence of statistically significant differences in a set of brain-to-brain co-regulation indices—primarily, PLV measure—between dyads of caregivers and VPT compared to FT infants. Previous research gave evidence of specific markers of lower co-regulation in behavioral synchrony (Montirosso et al., 2010), physiological coupling (Feldman and Eidelman, 2007; Porges et al., 2019), and neuroendocrine attunement (Provenzi et al., 2019) in dyads of VPT infants during the first year of life. Consistently, we hypothesized that VPT infants and their caregivers would show less strong brain-to-brain co-regulation indices compared to dyads of FT counterparts at 9 months (corrected age for prematurity, CA).

The second specific aim (Aim 2) is to investigate the effect of an early VF intervention for parents of VPT infants on the selected indices of brain-to-brain co-regulation at 9 months CA. By comparing EEG-hyperscanning-derived indices of inter-brain coupling between dyads of VPT infants exposed to the VF intervention and dyads exposed to care as usual during the 3 months following NICU discharge, we hypothesize to describe greater brain-to-brain co-regulation in the former group.

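### Aim 2 is the randomised VPT-VF versus VPT-CU comparison, but both its test and its sample size rest on a three-group ANOVA that includes the non-randomised full-term group and names no VF-CU contrast

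*Protocol article*

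**What the plan says.** *General and specific aims* defines Aim 2 as a comparison of "dyads of VPT infants exposed to the VF intervention and dyads exposed to care as usual during the 3 months following NICU discharge" and gives it a direction: "we hypothesize to describe greater brain-to-brain co-regulation in the former group". The same section expects VPT dyads to show weaker co-regulation than FT dyads (Aim 1) and names PLV as the leading index.

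Only VPT dyads are randomised. The abstract says "the former will be randomly allocated to one of two arms: VF intervention or care as usual". *Study design and procedures* nevertheless states "The 2-BRAINED project is a randomized-controlled trial (RCT) with three arms" and describes the FT group this way: "The third arm includes FT infants and their caregivers and will act as an additional control group unmatched by preterm conditions".

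The Aim 2 analysis is: "Separate analyses of variance (ANOVA) will be used with dyadic brain-to-brain co-regulation indices as the dependent variable and groups (FT, VPT-VF, and VPT-CU". The next sentence adds covariates: "Theoretically relevant (e.g., gestational age) and statistically identified (e.g., any variable significantly linked with the outcome variables) confounding variables will be controlled for". The section names no VF-CU contrast, post-hoc comparison or order of tests.

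*Statistical power and sample size estimates* ties the size of the trial to Aim 2, with f = 0.25, alpha 0.05, beta 0.20 and three groups. It reports 159 in total (53 per group), with 80 per group to be recruited.

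**The concern.** The F test of a three-level factor asks whether any of the three means differ. Aim 2 asks whether one particular pair differs, and that pair is the randomised one. If FT dyads score higher than both VPT groups, as Aim 1 expects, the Aim 2 test can reject with no VF effect at all. A significant result could then be reported under the Aim 2 heading as evidence for the intervention when it reflects term birth. The power statement shares the problem: 80% power for the three-group test is not 80% power for VF against CU.

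**Working it through.** **1. Reproduce the plan's figure.** Inputs from *Statistical power and sample size estimates*: f = 0.25, alpha = 0.05, power 0.80, k = 3. One-way omnibus F test, degrees of freedom (2, N - 3), noncentrality f² × N.
- N = 159: noncentrality 0.0625 × 159 = 9.94, power 80.5%.
- N = 156: power 79.7%.

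The smallest N divisible by three is therefore 159. The stated figure is arithmetically right, and it is the size for the three-group omnibus test.

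**2. What f = 0.25 implies for VF against CU.** It does not fix that difference, which depends on the pattern of means:
- VF equal to FT, CU lower: f = d√2/3, so d = 0.25 × 3/√2 = 0.53. A two-sided t test at 53 per arm has 77% power.
- Evenly spaced, VF midway: f = d√(2/3), so d = 0.25 × √1.5 = 0.31. Power is about 35%.
- VF equal to CU, only FT different: the FT gap is 0.53 SD and the VF-CU difference is 0.

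**3. Rejection by the omnibus test when VF = CU exactly.** The FT-VPT gap g is not in the document, so a range is assumed. Without covariates f = g√2/3:

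| FT gap (SD) | f | 53 per group | 80 per group |
|---|---|---|---|
| 0.3 | 0.141 | 33% | 48% |
| 0.5 | 0.236 | 75% | 91% |
| 0.53 | 0.250 | 80% | 94% |
| 0.8 | 0.377 | 99% | >99% |

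A VF-CU t test rejects 5% of the time in every row. Simulation at 0.53 SD agrees: 81% for the omnibus test and 5.2% for the contrast.

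**4. The same with gestational age as a linear covariate.** Assumptions: gestational age uniform over 28-35 weeks (VPT) and 37-41 weeks (FT), a step difference between FT and VPT, and 53 per group. By simulation with VF = CU, the adjusted group test rejects about 23% of the time at 0.53 SD (22% in a longer run) and about 45% at 0.8 SD. With no gap it rejects about 5%.

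**5. Power of the contrast that answers Aim 2.** For two groups f = d/2, so the same medium effect is d = 0.50. Two-sided t test at 0.05, noncentrality d√(n/2):
- n = 53: 0.50 × √26.5 = 2.57, power 72%.
- n = 64: 0.50 × √32 = 2.83, power 80%.
- n = 80: 0.50 × √40 = 3.16, power 88%.

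**The case against.** The strongest reply has three parts.

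First, this is a condensed article. Aim 2 is worded as VF against CU, and contrasts after an ANOVA are often left to a statistical analysis plan. That would excuse a missing detail. It does not cover this case, because the article fixes both the test and the sample size on three groups. A contrast added elsewhere would still leave 159 resting on a different test.

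Second, the model is adjusted. This stands as a limit on size: the unadjusted 75% and 99% do not describe a model containing gestational age. If the FT-VPT difference were wholly linear in gestational age, adjustment would remove it. With a step difference it does not. VPT infants (below 35 weeks) and FT infants (37 weeks or more) share no gestational ages, so the adjustment relies on extrapolation across the gap.

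Third, no FT gap is given. This also stands. A reader might infer that the test will reject whatever VF does, but at an unadjusted gap of 0.2 SD and 53 per group it rejects only 17% of the time.

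Two further inferences are tempting and are not supported:
- *Including FT dilutes a real VF effect.* With a VF-CU difference of 0.50 SD and 53 per group, unadjusted, the omnibus test has 75% power if FT equals VF, 75% if FT equals CU and 95% if FT is 0.25 SD above VF. The t test has 72%. The omnibus test falls below that (62%) when FT lies midway between CU and VF, an ordering the aims do not anticipate.
- *Aim 2 comprises 18 uncorrected tests with a 60% chance of a false positive.* Counting 3 indices × 2 bands × 3 episodes is an inference: the Aim 2 text does not say it runs by band and episode. The 60% (1 - 0.95^18) needs independent tests, whereas these indices come from the same recordings. PLV is already placed first.

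Calling FT an arm of the trial is loose labelling. The article makes clear elsewhere that only VPT dyads are allocated at random.

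**Conclusion.** The point holds. As written, the test assigned to Aim 2 does not test the Aim 2 hypothesis, and the sample size is correct for that test but not for the randomised comparison. With VF = CU and 53 per group, the chance of a significant Aim 2 result is 33% to 99% unadjusted for assumed FT gaps of 0.3 to 0.8 SD. It is about 23% (0.53 SD) to 45% (0.8 SD) with gestational age as a linear covariate, under the assumed age ranges and a step difference. The nominal level is 5%. These sizes depend on a gap the document does not state. The mismatch between aim, test and sample size does not.

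**What to change.** In *Specific aim 2*, state the primary analysis as the VPT-VF minus VPT-CU difference in PLV at 9 months corrected age, analysed as randomised, two-sided at 0.05 with a 95% confidence interval. Keep FT as a non-randomised reference group and, in *Study design and procedures*, describe the design as a two-arm randomised trial with an FT comparison group.

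In *Statistical power and sample size estimates*, restate power for that contrast. At d = 0.50 it is 72% with 53 analysable dyads per arm, 80% with 64, and 88% if all 80 are analysable.

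The cost is wording in these sections and a slightly less favourable power statement at 53 per arm. No extra enrolment is needed for 80% power provided 64 of the 80 per arm (80%) give usable data. The present plan assumes 53 of 80 (66%), and at that level the article should report 72%. No procedures or data collection change.
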